|                     | 
 
3. Cystic echinococcosis
 
4. Chagas disease
 
5. Cutaneous leishmaniasis
 
 
This list is not exhaustive and may evolve according to new emerging diseases or scientific advances. Whenever possible, collaboration with other existing or future similar initiatives will be explored at the Belgian or European level, to avoid any duplication of efforts.
                                                                                                                                                                                                                                                                                                                                                                                                                                                                                                                                                                                           |
| Register Population | 
All patients diagnosed with one of the selected tropical diseases in any Belgian or European medical institution are eligible for inclusion. As this study is purely observational (no intervention beyond optimal standard of care), no written informed consent will be requested in institutions where an optout strategy is put in place (for epidemiological surveillance and secondary use of clinical data). In other institutions, a written informed consent will need to be obtained. In both situations' scenarios, participation to Tropistry will be notified in the medical file at inclusion (usually during one of the follow-up visits).
 
There is no prespecified sample size calculation, since most diseases are rare, and coverage is still uncertain. However, it is expected to reach at least 100 inclusions per disease.
                                                                                                                                                              |

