### 5.3. REGISTER POPULATION

For this register, there is no defined upper limit to the number of patients to be recruited. It is expected that at least 100 inclusions should be obtained per disease to allow some robust analysis leading to clinical recommendations.

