## 5.6. STATISTICAL ANALYSIS

The international register will be analyzed annually to produce descriptive statistics on different variables including patient safety, patient demographics, details on diagnosis and administered treatments. Clinical outcomes and the follow-up of patients will also be assessed. Association between specific treatment strategies and patient safety/patient-related parameters will be analyzed using analysis of variance or Student's t-test for the continuous variables (or equivalent non-parametric tests for non-normally distributed variables Mann–Whitney U test or Kruskal-Wallis test) and the chi-square tests or Fisher's exact test for the categorical variables as well as multivariable regressions. Time to event analysis, by using Kaplan-Meier and Cox proportional hazard models will be performed to examine factors associated with the clinical outcomes. All statistical analyses will be performed using STATA, Python, and/or R statistic software and will be performed by trained personnel (epidemiologist, statistician) using current methods of analysis.

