The treatment of acute schistosomiasis, either symptomatic (Katayama syndrome) or not, is even more challenging than its diagnosis. As the symptoms are mainly driven by the hypersensitivity reaction, corticosteroids need to be administered in diseased patients, but the optimal timing, dosage and duration are poorly established in the absence of randomized trials. It makes sense to associate the (currently unique) antischistosomal drug, praziquantel, to kill off the already matured schistosomes, but this treatment is largely ineffective against juvenile worms, partly responsible of the symptoms. Therefore, most of the time experts do not recommend praziquantel in the early phase of the acute infection, arbitrarily established within 6 weeks after infection, while it should/could be administered later on. But here again and for the same reason, the optimal timing and dosage of praziquantel to completely clear the infection are unknown, and many different regimens are in place according to local experience and expert-based guidelines. In addition, the interactions between corticosteroids and praziquantel are poorly understood but it appears that the blood concentration of the latter drug substantially decreases when co-administered with corticosteroids. Finally, the administration of praziquantel in asymptomatic, or mildly symptomatic, infected individuals may provoke in more than 50% of cases a serious clinical exacerbation (by antigenic release). Overall, there is no evidence regarding the optimal therapy of acute schistosomiasis, and a wide variety of regimens are proposed

even in specialized setting, as highlighted in 2019 by a survey of the European network of travel clinics, TropNet (unpublished data).

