These “recommendations” will of course evolve with the scientific advances and new knowledge (included that generated by Tropistry). It is important to highlight that each center may propose different therapeutic regimens, according to local/national guidelines. As of June 2024, based on the experience at ITM (current state-of-the-art at ITM; manuscript about a recent cluster being submitted), we will recommend in Tropistry the following therapeutic approach:

- In case of symptomatic acute schistosomiasis,
  - If diagnosis earlier than 6 weeks after exposure/infection: only methylprednisolone 0.5 mg/kg/day for 3 days, to be prolonged/repeated if unsatisfactory control of inflammatory symptoms
  - If diagnosis made later than 6 weeks after infection: praziquantel 40 mg/kg single dose, followed after 2-4 hours by methylprednisolone 0.5 mg/kg/day for 3 days, to be prolonged/repeated if unsatisfactory control of inflammatory symptoms (note that this interval allows the concentration peak of praziquantel within 1-2 hours after administration, with no drug interaction)

- In case of asymptomatic acute schistosomiasis (for example within a cluster of cases)
  - Diagnosis earlier than 6 weeks after infection: abstention
  - Diagnosis later than 6 weeks after infection: praziquantel 40 mg/kg single dose followed after 2-4 hours by methylprednisolone (to prevent any clinical exacerbation)

All patients with acute schistosomiasis (either symptomatic or not) will receive a second 40 mg/kg single-dose course of praziquantel at week 12 after infection (to clear all juvenile worms which have meanwhile become adults). Here there is a large consensus between experts.

As already highlighted, the purpose is to make Tropistry as accessible as possible for busy clinicians confronted with any of the target diseases. For pragmatic reasons, inclusion and data entry will be retrospective (with reasonable delay of 6 months after initial diagnosis), and considered as secondary use of clinical data for institutions where an optout strategy is in place. This will be the case with most partners for this first phase of the project focusing on acute schistosomiasis. In other settings, a formal written informed consent will be requested for each included patient.

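### For continuous variables the protocol names equal-variance tests (Student's t-test, ordinary ANOVA) to compare non-randomised treatment groups of probably unequal size; the Welch versions would be safer (minor)

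*Protocol*

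**What the plan says.** Section 5.6 of the protocol, and in near-identical terms the Statistical Methods row of section 2, plans tests of association between treatment strategies and patient outcomes. For continuous variables it names "analysis of variance or Student's t-test for the continuous variables". The fallback is "equivalent non-parametric tests for non-normally distributed variables Mann–Whitney U test or Kruskal-Wallis test". Chi-square or Fisher tests cover categorical variables. The sentence ends with "as well as multivariable regressions", whose type is not given, and the work is left to trained personnel "using current methods of analysis".

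On group sizes, section 5.3 says only: "It is expected that at least 100 inclusions should be obtained per disease". Section 2 adds: "There is no prespecified sample size calculation, since most diseases are rare". No significance level, split between treatments or SD appears anywhere.

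On how treatment is chosen, section 8 says of praziquantel that "many different regimens are in place according to local experience and expert-based guidelines", and of the register that "each center may propose different therapeutic regimens, according to local/national guidelines". Section 9 ties local or systemic therapy for leishmaniasis to simple or complex disease.

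**The concern.** Student's t-test and ordinary ANOVA pool the within-group variances. If groups differ in both size and spread, the pooled variance is dominated by the larger group and the standard error of the difference is wrong. When the smaller group is the more variable one, the standard error is too small and false differences appear too often. When the larger group is the more variable one, the standard error is too large and real differences are missed.

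A non-randomised register is where unequal group sizes should be expected: one common regimen against several rarer ones. Unequal spread is plausible where treatment follows severity, although the protocol does not document it. The stated fallback does not cover this case, because a variable can be normal within each group and still have unequal variances. At stake are the comparisons of means that the annual analyses may report in support of treatment recommendations.

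**Working it through.** The protocol gives no figure to reproduce, so this is a check of how the named tests behave.

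**Inputs**
- Total N = 100: the expected minimum per disease in section 5.3.
- Two-sided 5% level: assumed.
- Group splits from 50/50 to 90/10: assumed.
- SD ratio from 1 to 3, in either direction: assumed.
- Normal data with equal means, unless stated otherwise.

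**Large-sample formula for Student's test**
- s_p² = [(n1−1)s1² + (n2−1)s2²] / (n1+n2−2)
- V_pooled = s_p²(1/n1 + 1/n2), the variance that the test uses
- V_true = s1²/n1 + s2²/n2, the actual variance of the difference
- Type I error ≈ 2[1 − Φ(1.96·√(V_pooled/V_true))]

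**Three cases worked through**
- 70/30, SDs 1 and 1.5: s_p² = (69 + 29×2.25)/98 = 1.370; V_pooled = 1.370×0.0476 = 0.0652; V_true = 1/70 + 2.25/30 = 0.0893; 1.96·√0.731 = 1.675; error 9.4%.
- 80/20, SDs 1 and 2: s_p² = (79 + 19×4)/98 = 1.582; V_pooled = 1.582×0.0625 = 0.0989; V_true = 1/80 + 4/20 = 0.2125; 1.96·√0.465 = 1.337; error 18.1%.
- 80/20, SDs 2 and 1: s_p² = (79×4 + 19)/98 = 3.418; V_pooled = 0.2136; V_true = 4/80 + 1/20 = 0.100; 1.96·√2.136 = 2.865; error 0.4%.

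**Simulation, two groups** (40,000 replicates for 85/15 and 100,000 for the rest; 30,000 for Mann-Whitney)

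| Split | SD, larger : smaller group | Student | Welch | Mann-Whitney |
|---|---|---|---|---|
| 50/50 | 1 : 2 | 5.1% | 5.1% | 5.8% |
| 80/20 | 1 : 1 | 4.9% | 5.1% | 5.0% |
| 60/40 | 1 : 1.5 | 7.0% | 5.0% | 6.3% |
| 70/30 | 1 : 1.5 | 9.3% | 5.0% | 7.1% |
| 80/20 | 1 : 2 | 18.1% | 5.1% | 11.0% |
| 85/15 | 1 : 2 | 21.1% | 5.0% | not run |
| 80/20 | 2 : 1 | 0.5% | 5.1% | 1.5% |

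Over the whole grid (50/50 to 90/10, SD ratio up to 3, both directions) Welch stayed between 4.9% and 5.3%. Student reached 36.7% at 90/10 with three times the SD in the smaller group, and about 0% in the reverse case.

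**Three groups, ordinary ANOVA** (50,000 replicates)
- 60/25/15 with SDs 1/1.5/2: 14.9%.
- 70/20/10 with the same SDs: 19.6%.
- 70/20/10 with SDs reversed to 2/1.5/1: 0.9%.
- 34/33/33 with unequal SDs: 5.5-6.1%.

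Welch's ANOVA, simulated separately at the first three settings, stayed at about 5%.

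**Cost when variances are equal.** At 80/20, with a difference for which Student has 80% power, Welch has about 78%.

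**Skewed data.** With identical lognormal distributions (log SD 1) in both groups, Welch ran at about 7.8% at 80/20 and 9.5% at 85/15. Student and Mann-Whitney were at about 5%.

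**The case against.** The case for leaving the text alone has five parts.

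1. **Reach.** Section 4.1 defines safety by the frequency and pattern of adverse events, and effectiveness by a cure or stabilisation rate. Section 7.1 says that almost all data, laboratory values included, will be collected in categories. Those go to chi-square or Fisher tests. Days in hospital (section 5.5) stay numeric, but section 8 says that acute schistosomiasis rarely needs admission. That variable will be sparse and skewed, and section 5.6 already sends it to rank tests. All of this stands and is the main reason the point is minor. The text at hand does not list which variables stay numeric.

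2. **Assumed inputs.** A reader might infer that the planned tests will run at 18-21%, or below 1%. The documents do not support that. They give no significance level, split or SD, and nothing says that spreads differ between treatments. Those rates need about 80/20 or more together with a twofold SD ratio.

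3. **Other analyses.** Regression is planned as well, and analysts may use current methods. This helps only in part: ordinary linear regression makes the same equal-variance assumption, and a general phrase does not replace a named test.

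4. **Level of detail.** The choice between Student and Welch is often left to a statistical analysis plan, which may exist and is not shown. But here the protocol has made the choice, in two places.

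5. **The rank-test rule.** A reader might go further and make Welch the default for every continuous variable, with rank tests as secondary. The lognormal result argues against that: with skewed data and unequal groups, Welch itself exceeds 5%. Nor does the protocol prescribe a formal normality pre-test; non-normality can be judged from the nature of the variable.

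Confounding by indication affects an unadjusted difference in means whichever test is used, and this change does not address it.

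**Conclusion.** The point holds in a limited form and is minor. The protocol fixes equal-variance tests for groups that are likely to be unequal in size, and its only stated alternative responds to non-normality. Under the assumptions above, Student's error ranges from about 5% (equal groups or equal SDs), through 7-9% under moderate imbalance, to 18-21% under strong imbalance with a twofold SD in the smaller group. It drops below 1% in the reverse of that last case. Welch holds about 5% in all of these. Unequal group size follows reasonably from the design; unequal spread is an assumption. The primary measures are not affected. What is affected is the set of variables kept continuous and roughly symmetric, which looks small.

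**What to change.** In section 5.6 and in the Statistical Methods row of section 2, replace the pair of named tests by *Welch's ANOVA or Welch's t-test* for continuous variables that are roughly symmetric. Keep Mann-Whitney and Kruskal-Wallis, as now, for clearly skewed variables such as days in hospital.

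The cost is a wording change in two places, with no effect on data collection or patients. When variances are in fact equal, the loss of power is very small: about 78% against 80% at 80/20.

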## 4. OBJECTIVES

### 4.1. PRIMARY OBJECTIVE

To document the **safety** (frequency and pattern of adverse events) and **clinical effectiveness** (cure or stabilization rate at relevant timepoint) of current treatments for patients diagnosed with any of the selected tropical diseases (listed below\*) in Belgian and European hospitals and travel clinics.

1. Acute schistosomiasis
2. Neurocysticercosis
3. Chagas disease
4. Cystic echinococcosis
5. Cutaneous leishmaniasis

\*This selection is indicative and limited to parasitic diseases, based on the considerations described in the text, and may evolve according to the needs. Also, the extension of the registry to each disease will be progressively phased, following the proposed order.

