  - Administered antiparasitic and adjunctive treatment (in case different of recommended, request to explain the reason for deviation)
  - Description and timing of drug-related adverse event if any

- Need of treatment interruption and reason (availability, adverse event, disease progression...)
- Laboratory changes (Electrolytes, Creatinine, liver function panel, Platelet count, red blood cell count, hemoglobin, white blood cell count, neutrophils, leukocytes, eosinophil count)
- Frequency and timing of follow-up visits with specific findings, if any
- Treatment response regarding clinical features (disease progression vs. stabilization vs. cure), with day of assessment
- Treatment response regarding microbiological outcome: eradication, reduction of the parasitic load, with day of assessment
- If inpatient stay: days on normal ward, intermediate care, intensive care unit total, as a marker of morbidity
- In case of death, cause of death
- Additional information on the case can be entered as a narrative

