Follow-up, treatment failure, and scarring assessment have been standardized in the registry following recent international recommendations. Clinical response is now evaluated at predefined time points: Day 42 and Day 90 (initial cure assessments), 6 months (final cure), and optionally at 9–12 months to detect relapse (see Figure). Treatment failure is defined as <50% re-epithelialization or flattening by Day 42, or <100% re-epithelialization or flattening by Day 90, in line with the consensus reached in harmonized clinical trial methodologies for cutaneous leishmaniasis. In addition, scar outcomes are systematically assessed using a standardized grading (from no visible scar to severe disfigurement or functional limitation) and classified by type (e.g. flat, atrophic, hypertrophic, keloid, pigmentary alteration). This approach enhances comparability across sites and aligns with WHO/TDR and DNDi guidance for clinical evaluation of CL.

[figure not shown]

Based on Olliaro P et al. Harmonized clinical trial methodologies for localized cutaneous leishmaniasis and potential for extensive network with capacities for clinical evaluation. PLoS Negl Trop Dis 2018 12(1): e0006141.

As already highlighted, the purpose is to make Tropistry as accessible as possible for busy clinicians confronted with any of the target diseases. For pragmatic reasons, inclusion and data entry will be retrospective (with reasonable delay of maximum 6 months after initial diagnosis), and considered as secondary use of clinical data for institutions where an optout strategy is in place. In other settings, a formal written informed consent will be requested for each included patient.

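### The group-comparison tests ignore the order in clinical response and scar grade, although order-respecting rank tests are already named; a cheap improvement

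*Protocol*

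**What the plan says.** Section 5.6 sorts the comparisons of treatment strategies into two families. Continuous variables go to analysis of variance or the t-test, or to "equivalent non-parametric tests for non-normally distributed variables Mann–Whitney U test or Kruskal-Wallis test". Categorical variables go to "the chi-square tests or Fisher's exact test for the categorical variables as well as multivariable regressions". The Statistical Methods row of section 2 repeats the rule and applies it to safety and clinical effectiveness; section 5.6 itself speaks of safety and patient-related parameters. Neither place names a trend test, an ordinal test or an ordinal model.

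Two of the recorded outcomes are ordered categories:

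- Section 5.5 lists "Treatment response regarding clinical features (disease progression vs. stabilization vs. cure), with day of assessment".
- Section 9 (Specific aspects of the treatment registry) states that "scar outcomes are systematically assessed using a standardized grading (from no visible scar to severe disfigurement or functional limitation".

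Other outcomes are not ordinal. Section 4.1 defines effectiveness as a "cure or stabilization rate at relevant timepoint", which is a proportion. Section 9 makes leishmaniasis failure a yes/no outcome: "Treatment failure is defined as <50% re-epithelialization or flattening by Day 42, or <100% re-epithelialization or flattening by Day 90". Scar type, also in section 9, is nominal.

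The only size given is in section 5.3: "at least 100 inclusions should be obtained per disease to allow some robust analysis leading to clinical recommendations".

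**The concern.** A general chi-square or Fisher test returns the same p-value however the categories are permuted. On a scale with k levels, comparing two strategies, chi-square spends k − 1 degrees of freedom on what is usually a one-directional question: does one strategy push patients towards the better end? A rank test puts that question on a single degree of freedom.

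The protocol names suitable rank tests but attaches them to continuous variables. A moderate, consistent difference in response or scarring is therefore more likely to be reported as no association. A significant unordered result also does not say by itself which strategy did better, although the annual descriptive tables would partly make up for that. Efficiency matters here because these diseases are rare: section 8 reports about 5 acute schistosomiasis cases a year at the coordinating institute.

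**Working it through.** **Inputs from the protocol.** Three response levels (section 5.5); an ordered scar grade with no number of grades in the text available (section 9); at least 100 inclusions expected per disease (section 5.3). There is no power figure to reproduce, because section 2 states that no sample size was calculated.

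**Assumed inputs.** Two strategies, 50 patients each; two-sided 5%; a proportional-odds shift with odds ratio (OR) 2 to 3; four or five scar grades; several category distributions.

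**1. Check that needs no category distribution.** With all the signal in one direction, the noncentrality for 80% power on 1 df is (1.960 + 0.842)² ≈ 7.85. Power of a k − 1 df chi-square with the same noncentrality is P[χ²(k − 1; 7.85) > 5% critical value]:

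| Levels | df | Critical value | Power |
|---|---|---|---|
| ordered test | 1 | 3.84 | 80% |
| 3 | 2 | 5.99 | 70.9% |
| 4 | 3 | 7.81 | 64.5% |
| 5 | 4 | 9.49 | 59.5% |

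**2. Simulation at 50 versus 50.** Each cumulative probability c in the reference group is moved by odds′ = odds × OR, or divided by OR for a shift the other way. Example: response 20/30/50 has cumulative odds 0.25 and 1. At OR 2 these become 0.5 and 2, so the cumulative probabilities are 0.333 and 0.667 and the second group is 33.3/33.3/33.3. Pearson chi-square is compared with the tie-corrected Mann-Whitney test:

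| Scale (reference) | OR | Chi-square | Rank test | Gain (points) |
|---|---|---|---|---|
| Response 20/30/50 | 2 | 36.3% | 45.6% | 9.2 |
| Response 20/30/50 | 3 | 75.2% | 83.6% | 8.3 |
| Response 10/30/60 | 2.5 | 44.4% | 55.2% | 10.8 |
| Response 5/5/90 | 2 | 15.3% | 21.3% | 6.1 |
| Scar, 4 even grades | 2.5 | 53.1% | 70.4% | 17.3 |
| Scar, 4 even grades | 3 | 70.4% | 85.0% | 14.6 |
| Scar, 5 even grades | 2 | 29.2% | 48.6% | 19.4 |
| Scar, 5 even grades | 2.5 | 49.6% | 71.9% | 22.3 |

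(Some gains differ from the displayed powers by 0.1 through rounding.) Over OR 2 to 3 the gain is about 6 to 11 points for three levels, 14 to 18 for four and 19 to 23 for five. One skewed five-grade distribution reached 23.7. With no true difference both tests reject in about 4% to 5.5% of runs.

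**3. Wider inputs.** With OR 1.5 to 4 and splits of 50/50 or 70/30, the gain for three levels runs from 0.4 to about 11 points. The largest gain found was 31.2 points (skewed five-grade scale, 70/30 split, OR 3: 41.4% versus 72.6%).

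**4. Where the advantage reverses.** If the shift is not consistent along the scale, chi-square does better:

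- Response 20/30/50 against 20/10/70: chi-square 64.9%, rank test 35.2%.
- Response 20/30/50 against 35/10/55, with more patients in both extreme categories: chi-square 67.6%, rank test 6.5%.

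**The case against.** The strongest reply is that most of the treatment inference lies elsewhere. The primary effectiveness measure is a rate and leishmaniasis failure is binary; chi-square and Fisher suit both, and there is no order to lose. The same sentence adds multivariable regressions of open type, which could include an ordinal model, and the next provides "Time to event analysis, by using Kaplan-Meier and Cox proportional hazard models will be performed to examine factors associated with the clinical outcomes". In a non-randomized registry with many regimens, adjusted models should weigh more than crude tests. A statistical analysis plan, not shown, may also settle the test for each ordinal variable. Finally, 100 is an expected minimum per disease, not a 50-versus-50 comparison, and with sparse categories Fisher's test would normally replace the Pearson test simulated here.

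Much of this stands, and it limits the point. A reader might infer that every categorical outcome is left to an unordered test alone. The regressions and time-to-event models rule that out. A reader might also infer that the primary effectiveness comparison loses up to 23 points. It does not: that figure belongs to an assumed five-grade scar scale, in the leishmaniasis module only.

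What remains is that the protocol states an allocation rule rather than staying silent. The regressions are added to the categorical tests and do not replace them, and Kaplan-Meier and Cox models do not analyse a scar grade. Taken as written, the rule sends both ordered outcomes to tests that ignore their order.

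**Conclusion.** The point holds for two outcomes, in the group-comparison tests only: the three-level clinical response and the scar grade. On the assumptions listed (100 patients split 50/50, two-sided 5%, proportional-odds shift with OR 2 to 3), ignoring the order costs about 6 to 11 points of power for response. For scar grade it costs about 14 to 23 points, if that scale has four or five grades. None of these assumptions comes from the protocol. Varying them gives a loss of roughly 0 to 31 points under a consistent shift, and step 4 shows that the sign can change otherwise. This is a modest efficiency gain at almost no cost, not an error that invalidates the planned analysis.

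**What to change.** In section 5.6 and the Statistical Methods row of section 2:

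- Limit chi-square/Fisher to nominal and binary variables. These include the cure-or-stabilization rate, leishmaniasis treatment failure and scar type, which stay as they are and remain formally compared.
- Compare clinical response and scar grade with the tie-corrected Mann-Whitney test (two strategies) or Kruskal-Wallis test (more than two). When adjusting, use proportional-odds regression and report a common odds ratio.
- Show the full distribution over the categories by strategy.

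The cost is one or two sentences. The ordered categories are already collected and the rank tests already listed, so no new data or patients are needed. The downside is lower sensitivity to patterns that do not run consistently along the scale, and a proportional-odds assumption to check. Showing the full distribution lets a reader see where either matters.
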